## Methods

### Design

This study is a multi-center RCT with a baseline (T0; six weeks before treatment), pretest (T1), posttest (T2), and follow-up (T3; six weeks after treatment) design. The study will take place successively in four to five nursing homes in Thuringia, Germany. The participants will be randomly assigned to an intervention or a control group. Following T0, random allocation in a 1:1 ratio will be performed stratified by gender using a computer-generated randomization list for each nursing home. The randomization will be performed by a member of the study team not involved in the baseline assessment using the random number generator Random.org.

At four assessment points, the nursing staff will conduct external assessments (see trial flow diagram, Fig. 1). Additionally, the participants’ behavior will be observed during the intervention period.

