### Primary outcome measures

At all four assessment points, quality of life and problem behavior will be assessed via external assessment by the nursing staff using different questionnaires.

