### Procedure

Six weeks before the intervention starts (T0), the severity of dementia will be assessed with the Mini-Mental State Examination (MMSE, [37]). At the same time, the nursing staff will conduct the first external assessments by completing different questionnaires regarding quality of life and problem behavior of PwD as described above. If the respective nursing staff member conducting the external assessment is uncertain about his or her assessment, a member of the project staff will attend the case conferences in the nursing home to obtain the missing information.

At T0, additionally relevant personal data of the participating PwD (e.g. medication, other physical and psychological diagnoses) will be assessed. As part of the assessments at T1, T2, and T3, any changes in personal data will be recorded. After completion of T0, participants will be randomly assigned to IG and CG.

Following randomization, the individualized playlists of the preferred music will be created for participants of the IG. We will gather information from family members, nursing home staff, and directly from participants if they are able to verbalize their personal preferences. A questionnaire developed by the project team (based on Gerdner [38], Gerdner and Schoenfelder [39], and a search of popular music from different decades) including a list of examples of popular artists and song titles will be used to identify personally-relevant music for each participant. Additionally, a telephone or face-to-face interview will be arranged with family members and/or participants themselves to get more detailed information about their music preferences. Based on this information, up to three individualized playlists for each participant will be compiled. Standardized documentation sheets will be used to record the characteristics of each playlist (number of playlist, number of tracks, duration of compilation).

Further external assessments by the nursing staff regarding quality of life and problem behavior will be conducted directly before (T1) and after the intervention (T2). At posttest, acceptance and applicability of the music intervention will be assessed. The follow-up assessment will take place six weeks after the end of the intervention (T3).

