### Data analysis

The data will be analyzed using SPSS (IBM Corp., Armonk, NY) and R (R Development Core Team, Vienna, Austria).

Descriptive statistics of playlist characteristics, number of music sessions, music session duration, the proportion of cancelled sessions, and why sessions were cancelled will be reported as indicators of implementation quality.

To check whether the randomization was successful, baseline characteristics and the pre-test levels of the outcome measures will be compared between IG and CG. Further analyses will be adjusted for any potential significant differences.

“As randomized” analyses will be performed retaining participants in the group to which they were originally allocated regardless of protocol adherence. In addition, per protocol analyses will be conducted based on the sample of participants who adequately adhered to the intervention protocol by completing at least five out of the 21 music listening sessions. Any differences between protocol non-adherers and protocol adherers as well as dropouts and those who complete the study will be analyzed regarding baseline characteristics and pre-test levels of the outcome measures.

Multilevel models for discontinuous change [41] will be performed for the primary outcomes to evaluate whether outcomes show different change patterns between IG and CG from baseline (T0) to pretest (T1) to posttest (T2) to follow-up (T3). Following Göllner et al. [42], three contrast variables will be computed by subtracting the baseline values from pretest (T1-T0), posttest (T2-T0) and follow-up values (T3-T0), respectively. The multilevel models will have two levels: the four assessments of the outcome variables as level-1 and participants as level-2. To examine average treatment effects, group membership will be included in the multilevel models as a dichotomous level-2 predictor (0 = CG, 1 = IG). Differential effectiveness will be analyzed by including the severity of dementia and its interaction term with the group membership variable as person-level moderator variables. Full maximum likelihood estimation will be used to account for missing data.

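### The dropout and adherence comparisons use T1 outcome levels, which residents who leave between allocation and T1 cannot have; the T0 levels, collected before allocation, should be used

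*Protocol article*

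**What the plan says.** The Data analysis section plans two descriptive comparisons: protocol non-adherers against adherers, and dropouts against completers. Both use the same two sets of variables. For the second pair the wording is that "dropouts and those who complete the study will be analyzed regarding baseline characteristics and pre-test levels of the outcome measures".

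The Design section fixes the terms: "baseline (T0; six weeks before treatment), pretest (T1), posttest (T2), and follow-up (T3; six weeks after treatment) design". The Procedure section places allocation between the first two assessments: "After completion of T0, participants will be randomly assigned to IG and CG". It places T1 immediately before the music sessions start.

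The outcomes do not begin at T1. The section on the primary outcomes states: "At all four assessment points, quality of life and problem behavior will be assessed via external assessment by the nursing staff using different questionnaires". Other descriptive data are also taken at T0. The Procedure section lists the MMSE there and adds: "At T0, additionally relevant personal data of the participating PwD (e.g. medication, other physical and psychological diagnoses) will be assessed".

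**The concern.** A comparison of dropouts with completers is meant to show whether those who left differed from those who stayed. It works best on variables measured before anyone could drop out. Here the outcome levels named are those of T1, which is after allocation, so the comparison variable is itself lost to part of the attrition under study. The residents without it are the earliest leavers. In the intervention group they also completed none of the 21 sessions, so they are non-adherers under the threshold of five.

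At stake is how informative the outcome-level part is. If residents who leave early have, for example, more depressive symptoms or agitation than the rest, a comparison on T1 levels cannot show it and may look more reassuring than it should. That is useful background for a plan that handles missing data by full maximum likelihood and adds a per-protocol analysis.

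**Working it through.** **Step 1. Order of events** (Design and Procedure sections).

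| Event | Timing | Outcome scores held by a resident who leaves before T1 |
|---|---|---|
| T0 | six weeks before treatment | yes |
| Allocation | after T0, date not given | – |
| T1 (pretest) | directly before the intervention | no |
| T2 (posttest) | after the six-week intervention | no |
| T3 (follow-up) | six weeks after the intervention ends | no |

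That such a resident cannot enter a comparison on T1 levels follows from the design alone and needs no assumption. The same resident does have MMSE, medication, diagnoses and outcome scores from T0.

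**Step 2. The plan's dropout figure** (Sample size section). The 27% is the midpoint of the two cited rates: (18% + 36%) / 2 = 27%. Inflating the required 92 gives 92 / (1 − 0.27) = 126.03, so 127. The stated target of 130 is close to this and slightly above it. Expected dropouts among 130 are 130 × 0.27 = 35.1 (23.4 at 18%, 46.8 at 36%).

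**Step 3. How many leave before T1.** The article does not divide dropout by interval, so this step rests on assumptions. T0 to T1, T1 to T2 and T2 to T3 are about six weeks each, 18 in total. With d the total dropout proportion:

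- Even spread: 130 × d × 6/18.
- Constant hazard: 130 × [1 − (1 − d)^(1/3)].

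| Total dropout d | Dropouts | Before T1, even spread | Before T1, constant hazard |
|---|---|---|---|
| 18% | 23.4 | 7.8 (33%) | 8.3 (36%) |
| 27% | 35.1 | 11.7 (33%) | 12.9 (37%) |
| 36% | 46.8 | 15.6 (33%) | 18.0 (38%) |

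**Step 4. Varying the timing, which is the uncertain input.** At 27% total dropout:

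| Share of dropouts leaving before T1 | Residents |
|---|---|
| 10% | 35.1 × 0.10 = 3.5 |
| 20% | 35.1 × 0.20 = 7.0 |
| 50% | 35.1 × 0.50 = 17.6 |

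**Step 5. Effect of the choice of time point.** With T1 levels and the two patterns of step 3, 35.1 − 11.7 = 23.4 or 35.1 − 12.9 = 22.2 dropouts can enter the outcome-level comparison. With T0 levels all 35 can, provided that their T0 assessments were completed.

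**The case against.** Four points can be made for the plan.

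1. *Early leavers are not lost from the check as a whole.* A reader might infer that about a third of dropouts disappear from the attrition check. The text does not support that. The same sentence also compares baseline characteristics, which these residents have from T0. They are missing only from the outcome-level part. This objection stands in full.

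2. *Baseline characteristics may be meant to include T0 outcome scores.* The article calls T0 the baseline, and the Data analysis section uses the term baseline values for T0 scores when it builds its contrasts. On that reading nobody is lost, and the T1 comparison is an extra. The wording leaves this open. But the sentence lists outcome levels separately and ties them to the pretest, which the same section labels T1. If T0 outcomes are meant, the sentence should say so.

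3. *The share of one third is not a figure in the article.* This is correct. It comes from assuming even or constant-hazard dropout over 18 weeks. The article does not say that the 27% covers T0 to T3, and the follow-up windows of the two cited studies are not given. Six weeks is also the longest possible gap between allocation and T1, since the allocation date is not stated.

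4. *The check is descriptive.* Nothing in the article ties its result to an analysis set, a model or a conclusion. The multilevel model takes all four assessments with full maximum likelihood, so early leavers can still contribute their T0 scores. This stands and limits the weight of the point.

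One could add that T1 levels suit the adherence comparison because they describe residents just before sessions begin. That is a reason to keep them as well, but not to omit T0.

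**Conclusion.** The point holds in a limited form. As written, the outcome-level part of both comparisons cannot include residents who leave between allocation and T1, although the same outcomes are measured at T0. That much rests on the article's own definitions and sequence.

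The size rests on assumptions. At the stated 27% of 130, about 12 to 13 of 35 dropouts are affected if dropout is even or at constant hazard from T0 to T3, and about 4 to 18 if 10% to 50% of dropouts leave before T1.

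A reader might go further and conclude that the primary result is compromised. The article gives no ground for this: the primary effect estimate does not depend on the comparison. What is weakened is a supporting check on selective attrition and non-adherence. The change is a free improvement, not a correction on which the trial's validity depends.

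**What to change.** In the sentence on dropouts and non-adherers, name T0 levels of the outcome measures in place of pre-test levels, for both pairs of groups. Keep the T1 comparison as an addition, labelled as restricted to residents who reached T1.

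The cost is one phrase in the Data analysis section. T0 scores are already planned for every participant before allocation, so no further data, visits or staff time are needed.

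### Nursing home and gender, the randomisation strata, are left out of the primary model, which costs precision to the extent that change over time differs by home or gender

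*Protocol article*

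**What the plan says.** The Design section of the protocol article sets the allocation: "Following T0, random allocation in a 1:1 ratio will be performed stratified by gender using a computer-generated randomization list for each nursing home". The strata are therefore home by gender. The same section adds: "The study will take place successively in four to five nursing homes in Thuringia, Germany". Each home thus has its own calendar period.

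The Data analysis section fixes the primary model: "The multilevel models will have two levels: the four assessments of the outcome variables as level-1 and participants as level-2". Group is a 0/1 predictor at level 2, and dementia severity with its interaction with group is added for moderation. The effect is read on change from T0: "three contrast variables will be computed by subtracting the baseline values from pretest (T1-T0), posttest (T2-T0) and follow-up values (T3-T0), respectively". Home and gender are named neither as levels nor as predictors. Other covariates enter through one rule, applied after comparing the arms at baseline and pretest: "Further analyses will be adjusted for any potential significant differences".

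Two further between-group comparisons in that section have no baseline contrast: goal attainment, rated at T2, and the observation frequencies in each 20-minute period.

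**The concern.** When arms are balanced on a factor that predicts the outcome and the analysis then ignores that factor, its variance stays in the residual although the design has taken it out of the treatment comparison. The adjustment rule does not help. It acts only on imbalance, and stratification makes imbalance in home and gender unlikely. It therefore tends to leave out the very factors that the design used.

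There is a plausible route for this to matter here. Nursing staff rate the outcomes, so raters differ by home, and the homes run one after another. Rater drift, season or staffing changes between T0 and T2 would act on everyone in one home and not on those in another. What is at stake is precision and, if the arms are balanced within strata, a test that rejects less often than its nominal level. The treatment estimate is not biased.

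**Working it through.** **Inputs.** Alpha 0.05 and power 0.95 come from the Sample size section; a two-sided test is assumed, since the article does not state sidedness. The share q of the variance of change explained by home-by-time and gender-by-time effects is not given, so it is assumed to range from 0 to 20%. The plan has no figure of its own on this point to reproduce.

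**Step 1: which effects remain.** Write an outcome as participant effect + home effect + home-by-time effect + error. In T2-T0 the participant effect and the constant home effect cancel; the home-by-time effect does not. The same holds for gender, and for T1-T0 and T3-T0.

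**Step 2: standard error.** The ratio of unadjusted to adjusted standard error is 1/√(1−q). For q = 0.10 this is 1/√0.90 = 1.054.

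**Step 3: power.** With 95% power when adjusted, the expected test statistic is 1.960 + 1.645 = 3.605. Without adjustment, power is Φ(3.605·√(1−q) − 1.960). For q = 0.10 this is Φ(3.420 − 1.960) = Φ(1.460) = 0.928.

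**Step 4: type I error if the arms are balanced within strata.** This is 2·(1 − Φ(1.96/√(1−q))).

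| q (assumed) | SE larger by | Power, from 95% | Type I error, balanced strata |
|---|---|---|---|
| 0 | 0% | 95% | 5.0% |
| 0.01 | 0.5% | 94.8% | 4.9% |
| 0.05 | 2.6% | 94.0% | 4.4% |
| 0.10 | 5.4% | 92.8% | 3.9% |
| 0.20 | 11.8% | 89.7% | 2.8% |

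**Step 5: simulation of the T2-T0 contrast.** Each scenario had 4,000 trials without a treatment effect: 96 participants, 4 homes, exact 1:1 allocation within home by gender, person and residual variance 0.5 each. The variance of change is then 0.5 + 0.5 = 1 before any home-by-time effect.

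- Constant home variance 0.11 or 0.36, nothing varying with time: SE without versus with home and gender 0.203 vs 0.203, and 0.204 vs 0.204. Type I error was about 5%. There is no inflation.
- Home-by-time variance 0.05, 0.11, or 0.25 (the last with a gender-by-time effect): SE 0.207 vs 0.204, 0.212 vs 0.203, 0.222 vs 0.203. Type I error without adjustment was 4.1%, 4.0% and 3.7%, with a Monte Carlo error of about √(0.04·0.96/4000) = 0.3 points.

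These home-by-time variances give shares of 0.05/1.05 = 0.05, 0.11/1.11 = 0.10 and 0.25/1.25 = 0.20. The simulated inflation is milder than in the table because only four homes are drawn, so on average (4−1)/4 of the home variance appears within a trial. For variance 0.11 this gives √(1 + 0.75·0.11) = 1.04, matching 0.212/0.203 = 1.04.

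**Step 6: comparisons without a baseline.** In a post-only comparison, constant home variance of 0.11 or 0.36 (with a gender effect) gave model SEs of 0.215 and 0.233 against true standard deviations of 0.205 and 0.203. Here constant effects do matter, by a factor of 0.215/0.205 = 1.05 or 0.233/0.203 = 1.15.

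**The case against.** **The covariate list may be left to the analysis plan.** Two levels are not an error in themselves, and the remedy keeps two levels. The article does not say that group and severity are the only predictors. This has some weight. But the article does state a rule for choosing covariates, and that rule points away from the strata. That is a choice made, not only a detail withheld.

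**A reader might infer that the standard errors are too large in any case.** The documents do not support this. On the change scale, constant home and gender effects cancel, and nothing in the article shows that home-by-time or gender-by-time effects exist or how large they are. Zero is within the range.

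**A reader might infer that the test is certainly conservative.** That needs near-exact balance within home-by-gender strata. The article mentions a computer-generated list and a random number generator but no blocks. With unrestricted lists the unadjusted test keeps about its nominal level and only precision is lost.

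**A reader might add that the trial is already short of power and loses 2 to 9 points more.** That takes d = 0.4 with N = 92, a correlation of 0.5 and a two-wave contrast: power 0.483 unadjusted against 0.503, 0.525 or 0.573 adjusted, at q = 0.05, 0.10 or 0.20. The article states neither the correlation nor that contrast. From its stated 95% power, the loss over the same range is about 1 to 5 points.

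**A reader might fear the opposite, as in a cluster-randomised trial.** Participants are randomised individually within homes, so that reasoning does not apply. One related caution stands. If the treatment effect itself varied between homes (assumed SD 0.3), the model SE would be too small for inference beyond these homes: 0.207 against a true 0.257, type I error about 11.5%. Fixed home terms do not cure this.

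**The extra terms are not free.** This also stands, and is taken up with the fix.

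**Conclusion.** The point holds as a modest efficiency improvement. The design randomises within nursing home and gender, the stated model includes neither, and the adjustment rule will rarely bring them in. For the change contrasts, the cost runs from nothing to about 5% of the standard error for q up to 0.10, and about 12% at 0.20. From 95% power that is a loss of 0 to about 2 points, or about 5 at the upper end. All of this rests on an assumed q. A conservative type I error also requires balance within strata, which the article does not state. Goal attainment and the between-group observation frequencies are more exposed, because constant home effects remain in them too. No bias and, with a treatment effect common to all homes, no excess of false positives follows from the omission.

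**What to change.** In every primary multilevel model, prespecify nursing home (fixed effect, 4-5 levels) and gender as level-2 predictors together with their interactions with the three time contrasts. Main effects alone would not reach the change contrasts. In the between-group comparisons without a baseline (goal attainment, observation frequencies), include home and gender as covariates. Do this whatever the baseline significance tests show. Do not add nursing home as a third random level, since 4-5 homes are too few to estimate its variance reliably.

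The cost is wording and some degrees of freedom. With five homes there are 4 + 1 = 5 added predictors, each with a main effect and three interactions: 5 × 4 = 20 fixed parameters per outcome (4 × 4 = 16 with four homes). The plan names full maximum likelihood, which does not correct variance estimates for the number of fixed effects, so use REML or a small-sample degrees-of-freedom correction. State that the result then refers to the participating homes, since fixed home terms do not address a treatment effect that differs between homes.

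### If dropout depends on dementia severity and the music effect varies with severity, the group-only model gives the effect among residents who stay; reading it from the planned severity model avoids this

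*Protocol article*

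**What the plan says.** All of this is in the protocol article.

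- **Average effect (Data analysis).** The multilevel models have "the four assessments of the outcome variables as level-1 and participants as level-2". Then: "To examine average treatment effects, group membership will be included in the multilevel models as a dichotomous level-2 predictor". No other person-level predictor is named for this purpose.
- **Severity (Procedure; Data analysis).** It is measured before allocation: "Six weeks before the intervention starts (T0), the severity of dementia will be assessed with the Mini-Mental State Examination". Its use in the models is confined to moderation: "Differential effectiveness will be analyzed by including the severity of dementia and its interaction term with the group membership variable as person-level moderator variables".
- **Missing data (Data analysis).** The one stated method is this: "Full maximum likelihood estimation will be used to account for missing data". Sample size assumes 27% dropout.
- **Covariates (Data analysis).** After the comparison of the two arms at baseline and pretest: "Further analyses will be adjusted for any potential significant differences". Separately, "dropouts and those who complete the study will be analyzed regarding baseline characteristics and pre-test levels of the outcome measures", but no consequence for the model is attached to that comparison.

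**The concern.** Maximum likelihood gives valid estimates when missingness is random given what the model contains. Here that is group and the outcomes seen before dropout. Severity is outside the average-effect model, and neither safeguard brings it in. The covariate rule responds to differences between arms, so a variable that predicts dropout but is balanced between arms is never added. The comparison of dropouts with completers is descriptive.

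The trial enrols residents from mild to severe dementia. If the more severe leave more often and respond differently, the figure reported as the average effect describes the severity mix of those who remained, not of those randomised. This is separate from chance imbalance and would persist with perfectly balanced arms.

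**Working it through.** **Inputs from the article (Sample size).** Dropout 27%; f = 0.2, which is d = 2f = 0.4 for two equal groups; 92 analysable residents; 130 recruited.

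**The plan's own figure.** 92 / (1 − 0.27) = 126.03, so 127, against 130 stated. The dropout allowance is consistent with the 27% used below. The point does not depend on how the 92 was reached.

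**Assumed inputs, not in the article.** Severity S is standard normal. Dropout follows logit p(S) = a + ln(OR) × S, the same in both arms, with a chosen so that overall dropout is 0.27. OR is 1.5 or 2 per SD of severity. The effect is 0.40 at mean severity and changes by 0.2 or 0.4 SD per SD of severity.

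**Step 1: severity of those who stay.** Mean S among stayers = E[S × (1 − p(S))] / 0.73.

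- OR 1.5: a = −1.03, mean = −0.106 SD
- OR 2: a = −1.10, mean = −0.172 SD

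**Step 2: shift in the estimate.** Size of shift = slope × distance of the stayers' mean from zero.

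| OR per SD | Slope 0.2 | Slope 0.4 |
|---|---|---|
| 1.5 | 0.2 × 0.106 = 0.021 | 0.4 × 0.106 = 0.042 |
| 2 | 0.2 × 0.172 = 0.034 | 0.4 × 0.172 = 0.069 |

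Against d = 0.4 this is 0.021/0.4 = 5% to 0.069/0.4 = 17%. The sign depends on the slope. If the effect falls with severity the estimate is too large; if it rises, too small.

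**Step 3: does maximum likelihood on the observed outcomes undo this?** Checked by large-sample simulation. The T2 outcome was regressed on group and the T0 and T1 outcomes among those observed, the large-sample equivalent of maximum likelihood under monotone dropout. The true effect was 0.40, falling with severity.

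- Slope 0.2, OR 1.5 and 2: group-only estimate about 0.42 and 0.43.
- Slope 0.4, OR 1.5 and 2: about 0.44 and 0.47.
- Severity plus severity × group, read at the mean of all randomised: 0.40 in every case.

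The T0 and T1 outcomes recovered essentially nothing here. They enter identically in both arms, so they cannot re-weight an effect that differs by severity.

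**Step 4: is a main effect of severity enough?** Under stronger assumed dropout (log-odds 1.2 per SD, OR about 3.3) and slopes of 0.1 / 0.2 / 0.4, the group-only model gave about 0.43 / 0.45 / 0.51. Adding severity as a main effect left these unchanged. Adding the interaction as well returned about 0.40.

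**Step 5: when the conditions fail.**

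- Constant effect, same severity-dependent dropout in both arms: 0.40, no shift, at severity–outcome correlations of 0, 0.3 and 0.6.
- Constant effect, severity-dependent dropout in the intervention arm only (log-odds 1.2 per SD): 0.376 and 0.368 at correlations of 0.3 and 0.6, against 0.319 and 0.242 for completers only. Maximum likelihood removes much of this bias. What remains is not toward the stayers' effect, which is 0.40.

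**The case against.** The strongest reply is that the bias with equal dropout patterns needs two things the article does not establish. It gives one overall dropout figure and nothing by severity. It plans to examine differential effectiveness, but its hypotheses do not include moderation by severity. A reader might infer that maximum likelihood cannot allow for severity-dependent dropout at all, or that the average effect is bound to shift. Neither is supported: Step 5 shows no shift with a constant effect and equal dropout patterns, and substantial recovery when dropout is arm-specific. A reader might also infer that leaving severity out as a covariate is the fault. Step 4 shows that adding it as a main effect alone would not help when the effect varies.

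The size is also modest. With about 130 × 0.73 = 95 stayers, an unadjusted group difference has a standard error near 2/√95 = 0.21 SD, so a shift of 0.02 to 0.07 SD is roughly 0.1 to 0.35 of a standard error.

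Finally, a group-by-time likelihood model is a standard choice, and centring and sensitivity analyses are commonly left to an analysis plan. That stands as far as silence goes. But the article does state which predictor yields the average effect and places severity in a different analysis, and its covariate rule would not bring in a dropout predictor balanced between arms. The choice as written can be improved.

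**Conclusion.** The point holds in conditional form and is minor. With the same dropout pattern in both arms, the group-only model estimates the effect among residents who stay if dropout depends on severity and the effect varies with severity. The plan treats the second as an open question by testing it; the first is an assumption that the article does not quantify.

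The shift of 0.02 to 0.07 SD (5% to 17% of d = 0.4) rests on the assumed odds ratios, slopes and a normal severity distribution. It should not be presented as an upper bound softened by the T0 outcomes, since in the simulation they did not reduce it. With a constant effect and equal dropout patterns, including severity brings only precision: a correlation of 0.2 to 0.3 between severity and change would cut residual variance by 0.2² = 4% to 0.3² = 9%.

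**What to change.** State in advance that the average effect is read from the severity model already planned. Include T0 MMSE, centred at the mean of all randomised residents, with its interactions with group and with the three time contrasts, and report the group effect on each contrast at that mean. A severity main effect alone is not enough. Report the model without severity as a sensitivity analysis. If an analysis plan already says this, nothing more is needed.

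The cost is one sentence. The value is already collected and the model already intended. It uses at most eight fixed-effect terms (severity 1, by contrasts 3, by group 1, by group and contrasts 3). In one simulated scenario with 130 residents, the standard errors with and without the severity terms were within 0.005 of each other (0.163 and 0.168). The main downside is the assumption that the effect changes linearly with MMSE.
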